- Meningitis, date of onset, indicate if csf culture positive
- Surgery
  - none
  - minor, specify if herniotomy, vp-shunt implantation, DA-ligation
  - major, specify
- Haemangioma
- ROP, if yes indicate maximum grade and if Plus disease
  - intervention, if yes specify if laser therapy or other
- Other secondary diagnoses
- Blood transfusion record, only EC-transfusion, if yes indicate amount
- Death
  - Date of death
  - Cause of death
  - Autopsy, if yes summarize the main findings

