### 10.1 Definition of (Serious) Adverse Events

#### Adverse events

Adverse events (AEs) are defined as any untoward medical occurrence in a patient or clinical investigation subject administered a pharmaceutical product and which does not necessarily have a causal relationship with this treatment. An AE can therefore be any unfavourable and unintended sign (including an abnormal laboratory finding), symptom, or disease temporally associated with the use of a medicinal study product, whether or not related to the medicinal study product. An AE may also consist of a new disease, an exacerbation of a pre-existing illness or condition, a recurrence of an intermittent illness or condition, a set of related signs or symptoms, or a single sign or symptom.

AEs observed by the investigator and/or reported by the caregivers or parents must be reported in the eCRF during the entire study period, the period of time from the first drug administration until discharge home.

For all AEs, sufficient information will be pursued and/or obtained so as to permit an adequate determination of the outcome of the event (i.e., whether the event should be classified as an SAE) and an assessment of the causal relationship between the AE and the investigational drug or study treatment(s).

Whenever available, the underlying disease or condition for which a therapeutic or diagnostic procedure is required should be reported as the AE term. Surgeries or other invasive procedures that had already been planned prior to the start of the study do not have to be documented as AEs. These planned procedures will be recorded in the eCRF by the investigator at the baseline visit. It is not important if the condition was known before enrolment, only if the procedure was planned before.

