This trial enrolls highly vulnerable and largely immature neonates who are born very preterm and thus are unable to survive without intensive care support. Most organ functions are physiologically immature in the neonatal period. The degree of immaturity is aggravated due to prematurity. Prematurity is characterized by the absence of abilities a healthy born infant has a priori when born at term. These abilities include but are not limited to body water homeostasis, body temperature maintenance, skin vulnerability, stable breathing and heart rate, drinking, digestion, liver function, and host defense (Guideline on the investigation of medicinal products in the term and preterm neonate, EMA, June 2009, Doc. Ref. EMEA/536810/2008). Therefore, the preterm body shows a large number of different symptoms which are characteristic hallmarks of immaturity and which disappear gradually alongside maturation over a timespan of many weeks, see also the below given short list of symptoms typically present in all very preterm infants (further information is given e.g. in the textbook edited by Maier RF and Obladen M, Neugeborenenintensivmedizin – Evidenz und Erfahrung, Springer 2011).

In addition to this immaturity there are various signs, particularly affecting the skin, owing to intensive care and fixation of life saving devices mainly on the skin by plasters, stripes and patches. These devices include but are not limited to breathing tubes, feeding tubes, intravenous lines, electrodes and sensors. As a result, mainly the immature skin shows transient signs of fixation and positioning as listed below.

In conclusion of both, large immaturity and intensive care, all very preterm infants are characterized by a variety of signs which are typical and expected in this population and must not be considered as an AE. To clarify this, there is in addition to the list of immaturity signs and intensive care signs a third list providing samples of AEs, which comprise common deteriorations of very preterm infants but which are not regularly expected and may indicate

therefore any unfavourable and unintended sign, symptom, or disease temporally associated with the use of a medicinal study product, whether or not related to the medicinal study product.

1) Examples of immaturity signs not qualifying as AE:

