- **Apnea and oxygen desaturations** occurring in all very preterm infants due to immaturity of brain and lung and are treated with caffeine, oxygen and if severe with respiratory support.
- **Episodes of bradycardia** occur in almost all very preterm infants often in combination with apnea and oxygen desaturation.
- **Edema** occurs in almost all very preterm infants after birth due to kidney immaturity and usually disappears within few weeks. Edema may affect the whole body if severe or only typical regions, such as eyes, hands and feet.
- **Jaundice** is usually present in the first and second week of very preterm infants due to liver immaturity.
- **Skin barrier damage** is the consequence of immature skin and may occur by simply lying on the skin or touching it. Skin of very preterm infants is highly vulnerable and in regard to treatment similar to that of burn victims.
- **Gastric residuals** are often present and mainly transient in the first weeks of life.
- **Hypothermia or hyperthermia** following inappropriate incubator temperature.

2) Examples of intensive care signs not qualifying as AE:

- **Local redness of the skin** occurs always after removal of e.g. plasters, sensors, strips and is visible for few hours but sometimes for days.
- **Local trauma of the skin including local haematoma** is unavoidable when performing a heel prick, vein puncture or other medically needed invasive procedures braking skin integrity. Afterwards the damage is visible for few hours but sometimes for days.

3) Examples of AEs:

- **Anaemia** needing blood transfusion (RBC-transfusion)
- **ROP** Grade: Mild: Grade 1 → **AE**  
Moderate: > Grad 1 or plus disease → **AESI**, see below  
Severe: needing intervention → **SAE**, see below
- **BPD** Grade: Mild: no AE  
Moderate: O2 < 30% mit 36. PMA → **AE**  
Severe: O2 ≥ 30% mit 36. PMA → **AE**  
Prolongation of hospitalization due to BPD beyond EDD (requiring any respiratory support because of BPD) → **SAE**
- **Posthaemorrhagic ventricular dilatation:**  
Moderate if ventricular dilation is > 97 centile → **AE**  
Severe if ventricular dilation is > 4 mm above 97th centile. → **AE**
- **Patent ductus arteriosus:** if medical treatment is required (not preventive) and/or surgical ligation
- **Incorrect drug applications**

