### Serious adverse event

A SAE is any untoward medical occurrence that at any dose

- results in death,
- is life-threatening,
- requires subject hospitalization or prolongation of current hospitalization,
- results in persistent or significant disability/incapacity, or
- any important medical event and any event which, though not included in the above, may jeopardise the subject or may require intervention to prevent one of the outcomes listed above.

Any other medically important condition that may be not immediately life-threatening or results in death or hospitalization but may jeopardize the subject or may require intervention to prevent one of the outcomes listed above should also usually (i.e. based on medical and scientific judgment) be considered serious. For example: intensive treatment at home for allergic bronchospasm; certain laboratory abnormalities (e.g. blood dyscrasias); convulsions that do not result in hospitalisation; development of drug dependency or drug abuse.

Examples of SAEs:

- **Sepsis**, if blood culture is positive
- **NEC and/or perforation**, If Bell stage  $\geq$  IIa (pneumatosis proven) and/or perforation even without signs of NEC (e.g. Focal Intestinal Perforation, FIP)
- **ROP**, if intervention is required
- **BPD**, if severity leads to prolongation of hospitalization beyond EDD
- **Death**

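### The example lists in protocol Section 10.1 conflict with the protocol's own AE and SAE definitions for severe apnoea of immaturity and for posthaemorrhagic dilatation needing intervention

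*Combined protocol and SAP*

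**What the plan says.** Protocol Section 10.1 counts as an AE any unfavourable sign or disease associated in time with the study drug, including "an exacerbation of a pre-existing illness or condition". Its SAE definition covers death, threat to life, hospital admission or a longer stay, and lasting disability. It also covers any event that "may jeopardise the subject or may require intervention to prevent one of the outcomes listed above".

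Three example lists sit beside these definitions.

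- **Signs of immaturity that are not AEs.** The introduction describes signs "which are typical and expected in this population and must not be considered as an AE". The first entry covers apnoea and desaturation attributed to immature brain and lung, which "are treated with caffeine, oxygen and if severe with respiratory support". Bradycardia is the next entry.
- **Signs of intensive care that are not AEs.** These are skin marks and are not at issue here.
- **Examples of AEs.** ROP has a top tier, "Severe: needing intervention", coded SAE. BPD becomes an SAE when it keeps the infant in hospital past the expected date of delivery. For posthaemorrhagic ventricular dilatation the two tiers are "Moderate if ventricular dilation is > 97 centile" and "Severe if ventricular dilation is > 4 mm above 97" (the 97th centile). Both are coded AE.

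Section 6.5 grades posthaemorrhagic hydrocephalus 0 to 3. Grade 2 means repeated but transient drainage and grade 3 permanent drainage such as a shunt. Neither grade appears in the Section 10.1 lists. The Visit 3 form in Section 6.6 has a surgery category "minor, specify if herniotomy, vp-shunt implantation, DA-ligation".

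**The concern.** Every infant enters this trial with an intraventricular haemorrhage, so progression to hydrocephalus needing drainage is a foreseeable serious complication. Section 4.1 places infants who need a shunt among the most severely affected. A site that works from the SAE definition would report such a case as serious. A site that works from the graded list would find only an AE code.

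For apnoea the difficulty is that the list removes the event before anyone assesses it. Section 10.3 has the investigator judge causality and seriousness of documented AEs. A sign that may not be recorded as an AE does not enter that review. The drug is injected over two to three minutes (Section 8.2), so a reaction presenting as apnoea, desaturation or bradycardia could be put down to immaturity by rule and never assessed.

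Three outputs depend on SAE status: the 24-hour report to the sponsor (Section 10.4), the monthly SAE export that the sponsor reviews (Section 10.4, safety signals), and the SAE half of the by-arm summary (SAP Section 7).

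**Working it through.** The check is textual. The plan states no figure on this point that could be reproduced.

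**1. The three graded conditions in the AE list**

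| Condition | Codes below the top step | Step to SAE | Named among SAE examples |
|---|---|---|---|
| ROP | AE; AE of special interest | Yes, on intervention | Yes |
| BPD | none (mild); AE (moderate); AE (severe) | Yes, on prolonged stay | Yes |
| Ventricular dilatation | AE (moderate); AE (severe) | None | No |

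Two of three have an SAE step. The BPD row matters. It codes the severe grade as AE and then adds a separate step for seriousness. An AE code on a severe grade is therefore not itself the fault; the fault for dilatation is that the seriousness step is missing.

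**2. Where a shunt case leads.** Section 10.1 asks sites to report the underlying condition, not the procedure, as the AE term. For a shunt the nearest listed condition is ventricular dilatation, coded AE. The SAE definition, through its intervention, disability or longer-stay criteria, can lead to SAE for the same child. Both readings are available from the same section.

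**3. Apnoea against the other rules**

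- AE definition (10.1): worsening or recurrence of an existing condition counts. The exclusion has no exception for worsening.
- Abnormal-finding rule (10.2): a finding that needs medical intervention or other therapy counts. The exclusion expressly includes episodes treated with respiratory support. This conflict is clearest for desaturation, which is measured.
- SAE definition (10.1): a life-threatening event counts. The exclusion states no upper limit of severity.
- Assessment (10.3): the review is of documented AEs and abnormal findings, so an excluded sign is not sent to it.

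The words about respiratory support belong to the apnoea and desaturation entry only. Bradycardia is excluded in a separate entry that says nothing about severity.

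**4. What can be recovered later.** Hydrocephalus grade is recorded at Visits 2 and 3 and surgery at Visit 3. For apnoea, the Visit 3 form holds only totals of ventilation and CPAP days, which cannot place an episode in relation to a dose, and SAP Section 2.2 lists neither as an outcome.

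**5. Effect on the comparison between arms.** Randomisation is blocked separately within each centre (protocol Section 8.3; SAP Section 1) and the trial is double-blind. Differences in coding between centres should then fall about equally on both arms. The result is lower sensitivity and counts that are hard to interpret, with no expected shift towards either arm.

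**The case against.** The strongest reply is that the lists are headed as examples and nothing says they take precedence. Section 10.1 requires enough information on every AE to decide whether it is serious, Section 10.3 repeats that step, and the SAE definition is open-ended. For dilatation this stands. A reader might infer that the worst hydrocephalus is capped at AE, but the text sets no cap. The quoted line grades ventricular width on ultrasound, and hydrocephalus needing drainage is left without a code.

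For apnoea the reply is weaker. The SAE definition does start from any untoward occurrence, the exclusion is tied to immaturity, and a sudden collapse after an injection is arguably neither typical nor expected. Suspected new risks that require safety measures must also reach the sponsor within 24 hours. So it would be too much to say that an acute reaction cannot be detected. But the exclusion is mandatory in form, names severe episodes and gives no exception, so a site that follows it literally records nothing.

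The safeguards are real. The monitoring board reviews AEs and not only SAEs (Section 10.6). The SAP shows the full AE list (Section 7) and compares hydrocephalus above grade 1 by arm, adjusted for baseline (Sections 2.2.3 and 5.2.2). An imbalance in hydrocephalus would still be seen in those analyses, though later than through expedited reporting.

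Three further inferences are not supported. Extension of the haemorrhage is in no list, but it is a worsening of an existing condition and so already an AE. The minor-surgery label for shunts is a form category that nothing links to seriousness. The haemorrhage row of the safety table in Section 4.6 comes from an earlier prophylaxis trial, has p = 0.41, and does not describe extension of an existing bleed.

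**Conclusion.** The point holds as an inconsistency that should be reconciled. For apnoea and desaturation of immaturity, a mandatory exclusion contradicts the AE definition, the SAE criteria and the abnormal-finding rule. For dilatation, the list omits the seriousness step that it gives to the other two graded conditions and leaves drained or shunted hydrocephalus uncoded.

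The consequence is limited to prompt visibility of these events as SAEs and to the comparability of SAE counts across the nine centres. It does not amount to loss of the hydrocephalus data or bias in favour of either arm. The second of these rests on blinding and on randomisation within centre working as planned.

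How many events are affected cannot be given, because the documents state no rate of CSF drainage or of severe apnoea and do not show how sites in fact coded such cases. If all sites already applied the SAE definition, the dilatation part would have no effect on the data.

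**What to change.** Reconcile the Section 10.1 lists with the definitions in the same section and with Sections 10.2 and 10.3, by three statements:

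1. The codes in the lists are minimum codes. Any listed event that meets an SAE criterion is an SAE.
2. Posthaemorrhagic dilatation has an intervention tier coded SAE, modelled on the ROP row.
3. The immaturity exclusion does not apply to an episode that meets an SAE criterion, or to new worsening after a dose. The sponsor should define what worsening is measured against.

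The SAP describes randomisation in the past tense, so new reporting rules may reach few infants or none. For those already discharged, identify hydrocephalus cases from the existing grade and surgery fields. Classify them by one rule, blinded to arm, before the safety table in SAP Section 7 is produced. The surgery field does not ask for a date, so some cases will need source documents to place them within the AE reporting period. Apnoea cannot be rebuilt from the eCRF totals; the report should state that limitation.

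The cost is a short amendment and site memo, some extra SAE forms, and a blinded review of a limited set of records. Under Section 10.4, added SAEs that are neither fatal nor SUSARs go to the ethics committee only in the annual report. SAE counts will look less favourable, and the report should say that this reflects uniform coding.

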### Adverse events of special interest

As adverse events of special interest (AESIs) we defined ROP grade 2 or > 2 or Plus disease without intervention. Although in the preventive EPO study, section 4.6, no differences were found between EPO and placebo treated infants regarding ROP, there is still some concern regarding the EPO treatment in preterm infants regarding ROP. To address this issue and to increase alertness within this EpoRepair trial we defined all moderate stages of ROP as AESI which will be reported to the sponsor according to the same rules as SAEs.

### Serious adverse event

A SAE is any untoward medical occurrence that at any dose

- results in death,
- is life-threatening,
- requires subject hospitalization or prolongation of current hospitalization,
- results in persistent or significant disability/incapacity, or
- any important medical event and any event which, though not included in the above, may jeopardise the subject or may require intervention to prevent one of the outcomes listed above.

Any other medically important condition that may be not immediately life-threatening or results in death or hospitalization but may jeopardize the subject or may require intervention to prevent one of the outcomes listed above should also usually (i.e. based on medical and scientific judgment) be considered serious. For example: intensive treatment at home for allergic bronchospasm; certain laboratory abnormalities (e.g. blood dyscrasias); convulsions that do not result in hospitalisation; development of drug dependency or drug abuse.

Examples of SAEs:

- **Sepsis**, if blood culture is positive
- **NEC and/or perforation**, If Bell stage  $\geq$  IIa (pneumatosis proven) and/or perforation even without signs of NEC (e.g. Focal Intestinal Perforation, FIP)
- **ROP**, if intervention is required
- **BPD**, if severity leads to prolongation of hospitalization beyond EDD
- **Death**

#### **Suspected unexpected serious adverse reaction (SUSAR)**

A serious adverse reaction, the nature or severity of which is suspected to be not consistent with the applicable IB.

#### **Safety Signals**

All suspected new risks and relevant new aspects of known adverse reactions that require safety-related measures.

As this is a phase III study details are given in the IB.

### **10.2 Recording of (Serious) Adverse Events**

The well-being of the subjects will be ascertained by medical caregiver when subjects are hospitalized and the parents when subjects are discharged. Clinical investigators and ultimately the protocol PI have the primary responsibility for AE identification, documentation, grading, and assignment of attribution to the investigational agent/intervention.

All observed or volunteered adverse drug events (serious or non-serious) and abnormal test findings, regardless of treatment group or suspected causal relationship to the investigational drug or study treatment(s) will be recorded in the patient file and subsequently in the eCRF.

Recording will be done from first study treatment DOL 5 (-2/+3 days) until discharge home. As an exception the defined AEs (ROP grade  $>1$  or Plus diseases, BPD if classified as severe at 36 PMA, and anaemia) will be recorded without time limit.

AEs or abnormal test findings felt to be associated with the study treatment(s) will be followed until the event (or its sequelae) or the abnormal test finding resolves or stabilizes at a level acceptable to the investigator.

An abnormal test finding will be classified as an AE if one or more of the following criteria are met:

- The test finding is accompanied by clinical symptoms.
- The test finding necessitates additional diagnostic evaluation(s) or medical/surgical intervention; including significant additional concomitant drug treatment or other therapy

**Note:** simply repeating a test finding, in the absence of any of the other listed criteria, does not constitute an AE.

- The test finding leads to a change in study dosing or discontinuation of subject participation in the clinical study.

All AEs, serious and non-serious, will be fully documented in the appropriate eCRF. For each AE, the investigator will provide the onset, duration, intensity, treatment required, outcome and action taken with the investigational product.

### 10.3 Assessment of (Serious) Adverse Events

The investigator will promptly review documented AEs and abnormal test findings to determine if

- the abnormal test finding should be classified as an AE,
- if there is a reasonable possibility that the AE was caused by the investigational drug or study treatment(s), and
- if the AE meets the criteria for an SAE.

The intensity of an AE will be assessed by the investigator as being

- mild (hardly noticeable, negligible impairment of well-being),
- moderate (marked discomfort, but tolerable without immediate relief), or
- severe (overwhelming discomfort, calling for immediate relief).

The assessment of causality to the study drug by the investigator is done according to the following definitions:

|                  |                                                                                                                                                                                                                                          |
|------------------|------------------------------------------------------------------------------------------------------------------------------------------------------------------------------------------------------------------------------------------|
| Unrelated | 

• The event started in no temporal relationship to medicinal product applied and

• The event can be definitely explained by underlying diseases or other situations.

             |
| Related   | 

• The event started in a plausible temporal relationship to medicinal product applied and

• The event cannot be definitely explained by underlying diseases or other situations.

 |

